#### Secondary outcomes

The secondary outcome measures include change in other clinical assessments, such as HAMD-17 (range 0-54), Montgomery–Asberg Depression Rating Scale (MADRS, range 0-60), Oxford Depression Questionnaire (ODQ, range 0–104), Young Mania Rating Scale (YMRS, range 0–60), Clinical Global Impression Scale (CGI, severity range 0–8; efficacy range 1–4; efficacy index range 0–16), Sheehan Disability Scale (SDS, range 1–90), Wisconsin card sorting test (WCST), and Stroop color–word test (SCWT) after 5 and 10 sessions. And biomarkers representing potential mechanisms associated with suicidal ideation and depressive symptoms, after 5 and 10 sessions. What is more, the clinical relevance of these chosen efficacy and side effects occurence is also included as one of the secondary outcomes.

### Sample size {14}

The sample size was calculated based on the data from Kalu et al. [22] and Boggio et al. [23]. In these studies, the active tDCS was assumed to be superior to sham tDCS in controlling depression with a conservative mean diference of 0.74 and standard deviation (SD)=25.8. We set the type 1 error, *α* (significance), and the a power at 80%. We used G power software (V.3.1.9.4) to calculate the sample size. The result indicated that a minimum of 30 patients per group are needed (a total of 60 patients). Considering the 20% drop-out rate, 75 patients are needed in our experiment. Finally, we planned to enrol 38 patients per group for a total of 76 included patients.

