### Trial design {8}

The design of the trial is a double-blinded, randomized, sham-controlled trial to test for the superiority of the active tDCS group versus sham group. MDD patients, who took no psychotropic drug at baseline or maintained actual pharmacotherapy for at least 2 weeks before the stimulation initiation and during the whole stimulation period, were included. Groups will be randomized through a random code generator software (REDCap) at ratio of 1:1 into one of the following two groups: tDCS group or sham group. The total study duration is 8 weeks (Fig. 1).

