### Outcomes {12}

#### Primary outcome

The primary outcome is defined as reductive ratio of BSI after 1 and 2 weeks, as well as, after 5 and 10 sessions.

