## Statistical methods

### Statistical methods for primary and secondary outcomes {20a}

Descriptive analysis will consist of means and SD for continuous variables and percentages for categorical variables. Data normality will be tested with the results expressed as mean ± SD or percentage, whenever appropriate. Non-parametric tests will be used if data were not normally distributed. Baseline variables will be compared between the groups using either the Student *t* test or chi-squared test (e.g., sociodemographic data, cognitive function data, biomarkers representing inflammatory mechanisms associated with suicidal ideation and MDD, response and remission rates between groups). To compare primary endpoint, a two-way ANOVA will be used considering group (intervention and sham-control groups) and time points (pre and post-intervention), followed by the Bonferroni post hoc test, in case of significant F ratios. Using a mixed-effects model for repeated measures to analyze change from baseline of BSI scores, time, and their interaction. We will also adopt pretreatment values (e.g., age, gender, baseline BSI, HAMD-17, CRP, and blood cells level) as covariates to correct the possible differences. An intention-to-treat analysis will be conducted, i.e., all participants, regardless of adherence to the intervention, will be included in the final analysis. All calculations will be performed using the R-softawre, and the significance level will be set at *P* ≤ 0.05.

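### The printed sample-size inputs (mean difference 0.74, SD 25.8) are incompatible with 30 per group at 80% power; 0.74 is probably a mislabelled standardised effect, and it comes from depression rather than BSI

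*Protocol article*

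**What the plan says.** The Sample size {14} section of the protocol article bases the calculation on two cited tDCS studies. It takes active stimulation to be superior to sham "in controlling depression with a conservative mean diference of 0.74 and standard deviation (SD)=25.8". It sets power at 80%, names the type 1 error without giving it a value, and reports using G*Power: "The result indicated that a minimum of 30 patients per group are needed (a total of 60 patients"). It then allows for 20% drop-out, reaches 75, and plans 38 per group, 76 in all.

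Other sections supply what this one omits. Trial design {8} describes 1:1 randomisation and a trial meant "to test for the superiority of the active tDCS group versus sham group". Statistical methods {20a} puts the significance level at P ≤ 0.05. Under Outcomes {12}, "The primary outcome is defined as reductive ratio of BSI after 1 and 2 weeks". The article gives no other planning difference or SD, does not call 0.74 standardised, and gives no planning value for BSI.

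**The concern.** Read literally, a difference of 0.74 against an SD of 25.8 is close to no effect, and no ordinary two-group comparison detects it with 30 per arm. So the sentence that justifies the size of the trial does not lead to the number it reports.

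The second difficulty is the outcome. The planning effect is for depression, while the trial is to be judged on suicidal ideation. With no BSI difference or SD stated, a reader cannot tell from the article what effect on the primary outcome the trial can detect. That matters most if the result is null: without knowing that the trial is sized for a large effect, a reader could take a non-significant result as stronger evidence against benefit than it is.

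**Working it through.** **Inputs.** Difference 0.74, SD 25.8, power 80%, 30 per group before drop-out, drop-out 20% (Sample size {14}). Allocation 1:1 (Trial design {8}). Alpha 0.05 (Statistical methods {20a}). Assumed, because the article does not say: two-sided test, two-sample t-test.

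**Step 1: the plan's figure from its printed inputs.**

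- Standardised effect: d = 0.74 / 25.8 = 0.0287.
- Normal approximation: n per group = 2 × [(1.960 + 0.842) / d]² ≈ 19,082.
- Noncentral t (the G*Power two-sample t-test): n = 19,082.5, so 19,083 per group.
- Power at these inputs, noncentral t with noncentrality d × √(n/2): 5.1% at 30 per group and 5.2% at 38 per group. Both are essentially the type 1 error rate.

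The stated 30 per group is not reproduced. The gap is a factor of more than 600 (19,083 / 30 ≈ 636).

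**Step 2: other readings that keep both numbers** (normal approximation, 80% power).

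| Reading | n per group |
|---|---|
| One-sided alpha 0.05 | 15,031 |
| One-sided alpha 0.10 | 10,960 |
| 25.8 is a variance (SD 5.08) | 740 |
| SD is 2.58, or the difference is 7.4 | 191 |
| Baseline-adjusted analysis, correlation 0.99 | 380 |

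None gives 30. With the SD held at 25.8, 30 per group would need a difference of about 0.736 × 25.8 = 19.0.

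**Step 3: 0.74 read as a standardised difference.**

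- Noncentral t, two-sided 0.05, 80% power: n = 29.66, so 30 per group.
- Power at 30 per group: 80.5%.
- At one-sided 0.05 the answer would be 24 per group, so the match is with a two-sided 0.05 test (equivalently one-sided 0.025).
- Drop-out: 60 / (1 − 0.20) = 75, made even as 38 per group = 76.

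Every later figure in the section follows. The SD of 25.8 does not enter.

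**Step 4: what the trial can detect, for an unadjusted two-sample t-test at two-sided 0.05.**

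| | 30 evaluable per group | 38 per group (no drop-out) |
|---|---|---|
| Smallest d with 80% power | 0.736 | 0.651 |
| Power at d = 0.5 | 48% | 58% |
| Power at d = 0.4 | 33% | 41% |

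The values 0.4 and 0.5 are illustrative; the article offers no BSI effect. The 38-per-group column departs from the plan's own 20% drop-out.

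**The case against.** The strongest reply is that this is a slip in labelling and not a miscalculated trial. Read 0.74 as Cohen's d and the section works through to 76, so 19,083 per group and 5% power describe a faulty sentence and say nothing about the trial's real power. That largely stands. A reader might infer from the literal figures that the trial has almost no power or that its enrolment is wrong; the article does not support this, because a simple reading recovers its numbers. Nor are the two inputs impossible: a difference of 0.74 and an SD of 25.8 can coexist, but they do not yield 30 per group.

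It can also be said that the article does not hide the source of the effect. That is correct: the section names depression openly. What it lacks is any statement that the effect is assumed to carry over to BSI. Whether 0.74 is conservative relative to the cited depression studies cannot be judged without them; the objection is only to extending that word to BSI.

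Finally, the sensitivity figures are for a plain t-test. The plan lists a two-way ANOVA and a repeated-measures mixed model with baseline BSI among the covariates, for which they are approximate. That is a fair caution.

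The reply does not remove the defect. The reading as Cohen's d is an inference that only the trial team can confirm. Nor does this turn on detail left to an analysis plan: the article prints inputs that contradict its own result.

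**Conclusion.** The point holds as a reporting error in the basis for the sample size. The printed difference and SD are incompatible with 30 per group at 80% power: they need about 19,083 per group and give about 5% power at 30 to 38. The likely explanation is that 0.74 is a standardised difference labelled as a mean difference, which gives 30 per group with 80.5% power and leaves the SD without a role. On that reading 76 is adequate for the stated aim, and correction would not lower the stated 80%.

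Separately, the planning effect is for depression and no BSI difference or SD is given, so the 80% applies to BSI only if the same standardised effect does. With 30 evaluable per group, effects below about d = 0.74 have less than 80% power.

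The conclusion assumes a two-sided 0.05 level and a two-sample t-test. The incompatibility does not depend on those choices, since none of the variants tried comes near 30; the match with d = 0.74 does.

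**What to change.** Check the saved G*Power record for what was entered.

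- **If 0.74 was entered as a standardised effect under the settings above,** restate the sentence along these lines: standardised mean difference d = 0.74, taken from depression outcomes and assumed to apply to BSI; two-sided alpha 0.05; two-sample t-test; 30 evaluable per group gives 80.5% power; 60 / 0.8 = 75, rounded to 76. Remove SD = 25.8 or explain what it refers to.
- **If it was not,** restate the inputs actually used, or the power that 30 per group delivers under them.

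In either case, give alpha and sidedness in the section itself, and do not describe the effect as conservative for BSI without BSI data. State that the smallest effect detectable with 80% power is d = 0.74 with 30 evaluable per group, and add the power at smaller effects for illustration (48% at d = 0.5 and 33% at d = 0.4, unadjusted t-test).

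The cost is a look at the calculation record and a change of wording. No change in enrolment is needed.

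### The sample-size sentence pairs a difference of 0.74 with an SD of 25.8, which cannot give 30 per group; 0.74 is probably a standardised difference that has been mislabelled

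*Protocol article*

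**What the plan says.** The Sample size section of the protocol article takes its planning effect from two earlier tDCS studies. It describes active stimulation as better than sham in controlling depression "with a conservative mean diference of 0.74 and standard deviation (SD)=25.8". No scale or unit is given for either number.

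The same section names a type 1 error without a value, "and the a power at 80" per cent, and the software: "We used G power software (V.3.1.9.4) to calculate the sample size". It names neither the test nor whether it is one- or two-sided. The reported output is: "The result indicated that a minimum of 30 patients per group are needed (a total of 60 patients"). Allowing for 20% drop-out raises this to 75, and 38 per group (76 in total) are to be enrolled.

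Two missing inputs can be found elsewhere. Under Statistical methods for primary and secondary outcomes, "the significance level will be set at *P* ≤ 0.05". Under Trial design, the aim is "to test for the superiority of the active tDCS group versus sham group", with allocation "at ratio of 1:1 into one of the following two groups".

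**The concern.** A mean difference and an SD given together are normally on one scale, and their ratio drives the sample size. Here the ratio is very small, yet the stated requirement is only 30 per group. Inputs and output stand in the same short paragraph and contradict each other. The journal's condensing of the protocol does not explain that, because both are printed.

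This is the article's only statement of the effect the trial is built to detect. As printed, it could mean a raw difference of 0.74, a standardised difference of 0.74 or, if the SD of 25.8 is real, a raw difference of about 19. These are very different targets, and a reader cannot tell which one the 80% power refers to.

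**Working it through.** **Inputs.** Difference 0.74, SD 25.8, power 80% and 30 per group come from Sample size. Alpha 0.05 comes from the statistical methods. Allocation 1:1 comes from Trial design. A two-sample t-test, two-sided, is assumed because the article states neither the test nor the sidedness; one-sided results are shown as well.

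**1. Reproducing the stated 30 per group.** Treat 0.74 as a standardised difference (SD = 1) and leave 25.8 unused.

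- Normal approximation: n per group = 2(1.96 + 0.8416)² / 0.74² = 15.698 / 0.5476 = 28.67, so 29.
- Noncentral t, the calculation G*Power makes for this test: 29.66, so **30** per group. This matches the article.
- Power by noncentral t: 80.5% at 30 per group and 88.9% at 38 per group.
- Drop-out: 60/0.8 = 75, and 30/0.8 = 37.5, so 38 per group and 76 in total. This also matches.
- One-sided tests: alpha 0.05 would need 24 per group, which does not match. One-sided 0.025 gives 30, the same as two-sided 0.05.

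**2. The figures as labelled.** Treat 0.74 and 25.8 as raw values on one scale.

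- d = 0.74 / 25.8 = 0.0287.
- n per group = 2(1.96 + 0.8416)² / 0.0287² (unrounded d) = about **19,080**, some 600 times the stated 30 (19,080/30 = 636).

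| Figures as labelled, alpha 0.05 | Two-sided | One-sided |
|---|---|---|
| n per group for 80% power | about 19,080 | about 15,030 |
| Power at 30 per group (t-test) | 5.1% | 6.2% |
| Power at 38 per group (t-test) | 5.2% | 6.4% |

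Other alpha values do not rescue it. The smallest requirement found was 10,960 per group, at one-sided alpha 0.10.

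**3. Working back from 30 per group.** At two-sided 0.05 and 80% power, 30 per group detects d = 0.736.

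- For a difference of 0.74, the SD would have to be 0.74 / 0.736 = about 1.01.
- For an SD of 25.8, the raw difference would have to be 0.736 × 25.8 = about 19.0, which is about 26 times the printed 0.74.

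**The case against.** The strongest reply is that this is a labelling slip and no more. G*Power's t-test routine works from a standardised difference. With 0.74 in that role, every sample-size figure in the section comes back exactly, so the simplest explanation is that a standardised difference was written up as a mean difference. Alpha is available from the statistical methods section, and two-sided 0.05 is consistent with 30. The SD of 25.8 may be a genuine value on a source study's scale, reported beside the standardised effect. That cannot be judged without the cited studies.

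Most of this stands, and it sets the limits of the point. A reader might infer from the literal figures that the trial has only 5% power, or that 76 patients is the wrong number. The document does not support either step: the 5% follows only if both figures are raw values on one scale, and the match at 0.74 points away from that. A reader might also conclude that SD = 25.8 is simply false, or that the interim looks will be distorted. The first cannot be settled from this document. For the second, the Interim analyses section describes no conditional-power or sample-size re-estimation step that would use these numbers.

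The reply does not repair the sentence. The article calls 0.74 a mean difference, attaches an SD that a standardised difference does not need, and nowhere says otherwise. The good match is evidence about what was done, not a statement of it.

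**Conclusion.** The printed inputs are inconsistent with the printed result. As labelled they imply d = 0.029, about 19,080 per group, and about 5% power at 30 per group. The stated 30, and with it 60, 75 and 76, reproduces if 0.74 is a standardised difference, with power of 80.5% at 30 and 88.9% at 38 per group.

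The supported conclusion is a probable mislabelling of the effect size together with an SD that does not fit it. The planned sample size is not shown to be wrong. This rests on a two-sample t-test, two-sided alpha 0.05 and 1:1 allocation, and on the inference that 0.74 was entered as Cohen's d. Only the sponsor's own records can confirm that.

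The point concerns the arithmetic of this one sentence. Whether an effect on depression is the right basis for a trial whose primary outcome is the BSI is a separate question. The error is worth correcting because it sits in the only stated detectable effect, but it is a reporting correction and not a demonstrated design fault.

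**What to change.** Check the original G*Power inputs and restate the sentence to match them.

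- **If 0.74 was Cohen's d:** say so. State two-sided alpha 0.05, 80% power and the two-sample t-test, giving 30 per group. Remove SD = 25.8, or explain which scale it belongs to. If it is kept, add that the detectable raw difference on that scale at 30 per group is about 19.
- **If both figures are raw values on one scale:** withdraw the 80% power claim, and state the power and the detectable difference that 60 to 76 patients deliver.

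The cost is one corrected sentence, and no change in enrolment is needed. The downside is that the detectable effect, once stated plainly, may look less favourable.

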## Assignment of interventions: allocation

### Sequence generation {16a}

Patients are randomly assigned to either of two groups—the active tDCS group or the sham tDCS group based on a computer-generated randomization scheme (REDCap) operated by the study staff, signed as group A or B. REDCap is an electronic data capture tool. The randomization program is set up by SC. When the baseline assessment is completed, their contact information is sent to the allocation team that will assign the participants to either group A or B. The allocation is randomized and computer generated. The randomization cannot be influenced by the person making it or any other person. Participants were not able to accurately guess what treatment they would receive. Clinician scales are administered by a trained and blinded study staff to ensure consistency. Moreover, we also checked the internal consistency for all psychiatrists involved in scale ratings with a kappa value of 0.89.

Two senior psychiatrists experienced with the MINI scale guarantee an accurate diagnosis. All patients who fulfil the inclusion criteria will be randomized. Randomization will be requested by the psychiatrists who are responsible for recruitment and clinical interview.

### Concealment mechanism {16b}

Personnel who are not blind to the treatment arm are responsible for the randomization process where REDCap is used. When a participant has been recruited for the study and baseline assessment has been conducted, the person responsible informs the assessor the result of randomization, group A or B, process via email. The actual intervention will be unknown to the researchers and clinicians. The randomized intervention allocation is concealed until the statistical analyses of the resulting data have been completed and conclusions have been drawn.

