### Implementation {16c}

Randomization is carried out by a staff member outside the research group who generates the allocation sequence and assigns participants to interventions.

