## Blinding

### Who will be blinded {17a}

Participants, care provider, investigator, and outcomes assessor are blind to the information about group allocation.

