### Responsibilities of TSC

YF, AD, and WH review the progress of study and necessary changes to the protocol to facilitate the smooth running of the study. The TSC will also ensure that the trial is conducted in accordance with the relevant principles and will provide overall supervision of the trial. All aspects of local organization (including recruitment, identifying potential recruits, obtaining consent, providing day to day support for the trial and medical responsibility of the patients) will be provided by the PI and YC. And the research coordinators (DL, FW, QH, WY, MZ, ZW, SS, SK, SC, SH, VY) will operate tDCS device, collect data, and follow-up the patients. The PI and the research coordinators meet weekly to oversee conduct and progress.

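### The assessor is emailed each patient's A/B group letter, an avoidable weakness in blinding, and the article gives conflicting accounts of who runs randomisation

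*Protocol article*

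**What the plan says.** On who knows the allocation:

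- Concealment mechanism {16b}: after baseline, "the person responsible informs the assessor the result of randomization, group A or B, process via email". The same section says that the people running randomisation are not blind to the arm, but that the actual treatment stays unknown to researchers and clinicians.
- Who will be blinded {17a}: "Participants, care provider, investigator, and outcomes assessor are blind to the information about group allocation".
- Sequence generation {16a}: "Clinician scales are administered by a trained and blinded study staff to ensure consistency".
- Intervention description {11a}: protocol A or B is set in the device software by a password holder from outside the research team, the team cannot get the password while the trial runs, and those giving the stimulation are blind.

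On who runs randomisation:

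- Sequence generation {16a}: a "computer-generated randomization scheme (REDCap) operated by the study staff, signed as group A or B". It adds "The randomization program is set up by" a person identified only by initials, and leaves the assigning to an allocation team.
- Implementation {16c}: "Randomization is carried out by a staff member outside the research group who generates the allocation sequence", and the same person assigns participants.
- Responsibilities of TSC: the research coordinators "will operate tDCS device, collect data, and follow-up the patients". The initials given in {16a} recur in this list of eleven.

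**The concern.** The scales in this trial call for judgement, and {16a} relies on blinded raters for the clinician scales. A two-letter code shared by everyone in an arm protects that blinding only while its meaning stays secret. Giving the letter to the assessor removes a layer of protection and, on the article's account, gains nothing, because the person who must act on the letter is the outside password holder in {11a}.

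If a rater came to associate a letter with active stimulation, later ratings of every patient with that letter could be affected. The likely direction would favour active tDCS, though nothing in the document demonstrates that.

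The randomisation accounts matter for a related reason. {16b} says that those who run randomisation know the arm. Whether any of them also treat or collect data therefore decides whether an unblinded person could be in contact with patients or ratings. {16a} and {16c} give different answers on who they are.

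**Working it through.** The article states no figure on this point, so the check sets the sections side by side.

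**1. Does the email fit the blinding statements?** {17a} covers information about group allocation, which is wider than the identity of the treatment. A patient's group letter is information about group allocation. Read literally, {16b} and {17a} conflict if the assessor in {16b} is an outcomes assessor. Read as blind to active versus sham, they can coexist. Either way they sit badly together and the wording should be settled.

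**2. What can the letter reveal?** By itself, only which patients share an arm. It does not say which arm is active, since {16b} and {11a} keep the key and the password from the research team. The email follows baseline assessment, so baseline scores are not at risk. The exposed ratings are those at weeks 1, 2, 4, 6 and 8.

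**3. How far would a confirmed break spread?** The planned total is 76 patients, 38 per arm, with two labels.

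- Shared A/B code: knowing the arm of one patient fixes the meaning of both letters. Patients exposed = all whose letter is known, up to 76.
- Participant-specific code: patients exposed = 1 of 76.

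These counts are conditional on a break. They are not a probability of a break or an estimate of bias.

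**4. How could a break occur?** Procedure for unblinding if needed {17b} allows an individual unblinding, which under a shared code would decode every known letter. Interim analyses {21b} gives the research team access to results on the primary endpoint once 30% and 70% of patients have completed 8 weeks. At the first look, 0.30 × 76 = 22.8, or about 23 patients, would be complete, leaving up to 76 − 23 = 53 with ratings still to come. The article does not say whether those results are shown by letter. If they were, they could suggest which letter is active.

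**5. Who runs randomisation?** {16a} has it "based on a computer-generated randomization scheme (REDCap) operated by the study staff"; {16c} puts both the sequence and the assignment with one person outside the research group. Both cannot describe the same arrangement unless the study staff in {16a} are outside the research group. Responsibilities of TSC makes that harder to sustain for the set-up role, because the matching initials belong to a coordinator who operates the device and collects data. If that is one person, and if setting up the program counts as running randomisation, the {16b} statement that such personnel are not blind collides with the {11a} statement that operators are.

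**The case against.** The strongest answer is that A and B are only labels. The sentence after the one quoted from {16b} keeps the real intervention from researchers and clinicians, and {11a} withholds the password. This stands: a reader might infer that the assessor is unblinded, and the document does not support that.

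Other stronger readings also fail:

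- **The same staff rate, treat and randomise.** No sentence says so. It has to be pieced together from matching initials, from coordinators who collect data, and from {18a}, where data collectors are trained in assessments. Setting up a REDCap program is not the same as running allocation, and collecting data can mean blood samples or forms.
- **The assessor in {16b} is certainly an outcome rater.** Who will take informed consent? {26a} has assessors obtaining consent, so the term is not confined to raters.
- **One correct guess reveals every arm.** A person who guesses does not know that the guess is right; only a confirmed break does this.
- **The sham is known to be distinguishable here.** The Discussion reports that finding for healthy volunteers who received stimulation, and says that its generalisability to depression is unknown. It does not concern raters.
- **The primary outcome is biased.** The article does not say how the BSI is administered, so an effect on it is not shown.

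What the objection does not answer is why the assessor should hold the letter at all, or how {16a} and {16c} can both be right.

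**Conclusion.** The point holds as an avoidable weakness in blinding plus an inconsistency on who runs randomisation. It is not evidence of unblinding.

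Its size is best put as exposure: given a confirmed break, up to 76 patients under the shared code against 1 under individual codes. The chance of a break and the resulting bias cannot be derived from the document.

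The first part assumes that some assessors who receive letters also rate outcomes, and that the two letters serve the whole trial, as the text indicates. The wording conflict between {16a} and {16c} needs no such assumption. The further possibility that someone not blind to the arm also treats or collects data rests on the matching initials denoting one person, and remains an inference. The change is worth making because it is specific and cheap.

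**What to change.** - In {16b}, send the letter only to the person outside the research group who loads the stimulation protocol, and to nobody who rates outcomes.
- For patients not yet randomised, replace A/B with participant-specific codes.
- Reconcile {16a} with {16c}: state that the outside staff member sets up and holds the REDCap scheme and neither treats nor rates. If practice has differed, report what was done.
- For patients already enrolled, have raters who do not hold the letters do the remaining ratings where feasible, and report who held the letters.

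The cost is a code list and some reassignment of roles among existing staff; with eleven coordinators listed, that looks feasible. The main limit is timing. Recruitment began in October 2022 and was due to finish in March 2024, and the article appeared in January 2024, so many patients probably already carry A/B letters and cannot be recoded retrospectively. For them the gain is confined to later ratings and to transparent reporting.
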